#### Data analysis

Incremental cost-utility ratios will be estimated for each country by calculating the ratio between the average difference in total costs of illness and the average QALY difference over 12 months. Stochastic uncertainty of incremental cost-effectiveness ratios will be assessed by non-parametric bootstrapping with 2,000 replications. The maximum willingness-to-pay (MWTP) necessary to cover 95% of the incremental cost-effectiveness ratio variance will be estimated by means of the cost-effectiveness acceptability curves [42]. In order to take into account the economic differences between participating countries, country-specific MWTP thresholds suggested by Woods et al. [43] and Leech et al. [44] will be applied.

Net monetary benefit regression models with random effects for the UPSIDES treatment, fixed country effects and fixed treatment by country interaction effects will be computed to estimate the impact of country-specific differences on cost utility [45]. Individual net monetary benefit values will be computed for each study participant by multiplying the individual country-specific QALYs with MWTP thresholds ranging from $0 to $50,000 (steps will be defined on the basis of results from the incremental cost-utility analysis and subtracting country-specific individual costs [45]). Marginal effects of the net monetary benefit regression models will be computed to estimate country-specific net monetary benefits for defined MWTP thresholds. Robust standard errors will be estimated to account for skew distribution of net benefit values [46, 47]. Results from the primary data incremental cost-utility analysis will be used to develop a decision tree model [48] to simulate cost utility and health budget impact of the UPSIDES intervention for each country over a 5-year time frame [49]. The sensitivity analysis will consider variance of programme coverage and equity of service access [50].

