#### Statistical analysis and power calculation

Analyses will start once baseline data has been collected and cleaned. Descriptive statistics will be produced for all outcome measures, and outcome trajectories from t_0_ to t_3_ will be examined via exploratory analyses. The intervention’s effect on primary and secondary outcomes will be tested by means of random-effect regression models including a fixed group effect over time, allowing the inclusion of cases with incomplete (unbalanced) data across panels [36]. Post-hoc analyses will examine early (at t_1_) and late (at t_3_) effects for primary and secondary outcomes. All outcome analyses will be performed on an intention-to-treat basis. Per-protocol analyses will be part of the process evaluation (see below).

Sample size calculation was performed for testing whether the primary outcome (social inclusion) at t_2_ is affected by allocation. For six study sites, three time points, and estimated panel attrition of 10% at each time point, *N* = 558 participants (*N* = 93 per site) will be needed to detect a small effect size (0.25 SD units) with a power of 0.80 at a two-tailed significance level of 0.05. Sample size calculation was performed using the RMASS program (www.rmass.org) for a three-level mixed-effects linear regression model for the analysis of longitudinal data, assuming a linear effect over time, compound symmetry for error variance covariance, a person-level covariance (Int, Cov, Slope) of 0.300, 0.150, 0.100, and a centre-level covariance (Int, Cov, Slope) of 0.050, 0.025, 0.020.

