### Cost-effectiveness analysis

#### Measures

Comprehensive societal costs of mental illness will be estimated for each participating country using an adapted version of the Client Sociodemographic and Service Receipt Inventory (CSSRI) [37] at t_0_ to t_3_. The CSSRI-UPSIDES will be adapted for use at all sites to assess mental health service use and productivity losses due to mental illness. If not already available, country-specific unit costs of health and social care services will be determined by investigating publicly accessible sources (price lists, catalogues of fees and charges), by expert interviews or by calculations of staff and capital costs for services used, drawing on the principles recently developed by the Global Health Cost Consortium in their reference case for global health costing [38]. All costs will be converted into USD ($) using purchasing power parities [39]. Quality-adjusted life years (QALYs) will be estimated using the EQ-5D 3 L at t_0_ to t_3_ as used in most multinational cost-utility studies [40] and being available in the languages of all study sites. As country-specific population-based value sets are not available for most study sites, QALYs will be estimated on the basis of the European EQ-5D visual analogue scale for all countries [41].

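### The country cost-utility ratios and the net-benefit regression name no baseline EQ-5D or baseline cost term, although both are measured at t0; adjusting would gain precision at no data cost

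*Protocol article*

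**What the plan says.** Under Cost-effectiveness analysis, Data analysis, the article sets the level of the estimate: "Incremental cost-utility ratios will be estimated for each country". It gets each ratio by "calculating the ratio between the average difference in total costs of illness and the average QALY difference over 12 months". Stochastic uncertainty "will be assessed by non-parametric bootstrapping with 2,000 replications". A second analysis uses "Net monetary benefit regression models with random effects for the UPSIDES treatment, fixed country effects and fixed treatment by country interaction effects". Neither sentence names a baseline covariate.

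Under Measures, the baseline values are available. For utility, "Quality-adjusted life years (QALYs) will be estimated using the EQ-5D 3 L at t_0_ to t_3"; for costs, the plan uses an "adapted version of the Client Sociodemographic and Service Receipt Inventory (CSSRI) [37] at t_0_ to t_3".

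The article never calls the differences raw or unadjusted, and it does not say that they are adjusted.

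**The concern.** A 12-month QALY computed as an area under the EQ-5D curve contains the baseline value, which treatment cannot have changed. Baseline utility also predicts the later values. If one arm starts higher by chance, part of that head start appears as an incremental QALY. Costs can behave in the same way, since earlier service use tends to predict later use.

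Randomisation is stratified by site only (Allocation), so within a country baseline utility and cost are balanced only by chance. The ratios are formed country by country, where arms are small. A ratio is also fragile when its denominator is noisy and may be near zero. The country results feed the acceptability curves and the 5-year decision tree model, so avoidable noise is carried forward into both.

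**Working it through.** **Arm sizes.** The article gives no precision figure for the economic comparison, so the only figure to reproduce is the arm size. 558 / 2 = 279 per arm and 279 / 6 = 46.5 per arm per site, which matches the 279 and 47 in Table 1. The Setting section places the six sites in five countries, two of them (Ulm and Hamburg) in Germany:

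- Uganda, Tanzania, Israel, India: about 46–47 per arm
- Germany: 2 × 46.5 = 93 per arm

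**Chance imbalance.** The standard error of a standardised baseline difference is √(2/n). This is 0.207 at 46.5 per arm and 0.147 at 93. Under normality, the probability that it exceeds 0.2 SD in either direction is 33% and 17%. Over the five countries, the probability of at least one such imbalance is 1 − (1 − 0.335)⁴ × (1 − 0.173) = 0.84.

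**Assumptions, because the document gives no values.** QALYs are trapezoid areas. The utility SD is σ = 0.25 (range 0.15–0.30) and equal at all visits. The correlation r is equal between all visits, 0.5 (range 0.3–0.7). There is no dropout.

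**Formulas.** With visits at 0, 4, 8 and 12 months, the trapezoid weights are 1/6, 1/3, 1/3, 1/6. Their squares sum to 2/36 + 2/9 = 0.278. On the standardised scale:

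- variance of the QALY: V = r + 0.278(1 − r)
- slope of the QALY on baseline utility: b = 1/6 + (5/6)r
- share of QALY variance explained by baseline: R² = b² / V
- SE of the baseline difference: σ√(2/n) = 0.25 × √(2/46) = 0.0521
- SD of the QALY difference carried over from baseline: 0.0521 × b
- SE of the QALY difference: unadjusted 0.0521 × √V; adjusted, that value × √(1 − R²)

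**Results at 46 per arm, σ = 0.25.**

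| r | b | V | R² | carried-over SD | SE unadjusted | SE adjusted |
|---|---|---|---|---|---|---|
| 0.3 | 0.417 | 0.494 | 0.351 | 0.0217 | 0.0367 | 0.0295 |
| 0.5 | 0.583 | 0.639 | 0.533 | 0.0304 | 0.0417 | 0.0285 |
| 0.7 | 0.750 | 0.783 | 0.718 | 0.0391 | 0.0461 | 0.0245 |

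The purely arithmetic share of baseline in the area is 0.0521 / 6 = 0.0087 QALY. The rest of the carry-over comes through the correlation.

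**Sensitivity.** Standard errors scale with σ. At r = 0.5 the fall is from 0.0250 to 0.0171 for σ = 0.15, and from 0.0500 to 0.0342 for σ = 0.30. The carried-over SD runs from 0.013 (σ = 0.15, r = 0.3) to 0.047 (σ = 0.30, r = 0.7).

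**Germany** (93 per arm, σ = 0.25): 0.0293 to 0.0200 at r = 0.5, 0.0258 to 0.0208 at 0.3, and 0.0324 to 0.0172 at 0.7.

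**In sample-size terms.** At r = 0.5, adjustment is worth a factor of 1 / (1 − 0.533) = 2.1 for the QALY difference. The factor depends on r, not on σ or n.

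**Costs.** No cost SD or correlation over time is given, so no gain can be computed.

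**The case against.** The strongest reply is that the plan has not ruled adjustment out. A regression-adjusted mean difference is still an average difference, and the net-benefit sentence may describe the effect structure rather than every covariate. A journal article may leave covariates to an analysis plan that is not shown. This stands in part: a reader might infer that the plan commits to raw differences, but that is an inference from silence. What remains is that the article fixes a formula, a list of regression terms and the number of bootstrap replications, and neither the formula nor the list includes baseline.

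A reader might also infer that the country ratios are biased or that their uncertainty is understated. The documents do not support this. Allocation is randomised 1:1 within site, so the unadjusted difference has no systematic baseline bias. Resampling patients carries baseline variability into the bootstrap distribution and the acceptability curves. The carried-over SD in the table is a component of the unadjusted standard error, not an addition to it. The bootstrap shows this noise, but it does not remove it or correct a point estimate from an imbalanced sample.

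Three limits also stand. Every figure beyond the arm sizes rests on assumed values. The calculation ignores dropout, although the power section allows 10% attrition at each time point. And this is an economic analysis, not the primary outcome.

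**Conclusion.** The point holds as a free improvement in precision. The estimator as described is valid but names no baseline term, while the data needed to adjust are already collected. For a single-site country, baseline EQ-5D adjustment would cut the standard error of the QALY difference by about a third (0.0417 to 0.0285) at SD 0.25 and correlation 0.5. Over correlations of 0.3 to 0.7 the cut is about 19% to 47%. The proportional gain is the same for Germany, from a smaller starting standard error. It rests on trapezoid QALYs, equal SD and correlation across visits, and no dropout. The size of the gain for costs is unknown.

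It would be too strong to say that baseline imbalance passes in full into the QALY difference. Its direct weight is 1/6, and anything beyond that depends on how strongly EQ-5D correlates over time.

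**What to change.** State in the economic analysis plan that, within each of the 2,000 bootstrap replicates (resampled within arm, and within site in Germany):

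- incremental QALYs come from a regression of QALY on arm and baseline EQ-5D
- incremental costs come from a regression of cost on arm and baseline CSSRI cost
- a site term is added for Germany only, since it has no role in the four single-site countries

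Form the ratios and acceptability curves from the adjusted differences, and add baseline EQ-5D and baseline cost to the net monetary benefit regression. If the full analysis plan already does this, one sentence saying so is enough. The cost is wording and some programming; no new data, visits or patients are needed.

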The peer support training has been manualised with a complementary workbook addressing underlying values and principles, specific skill training and preparing PSWs for tasks around recovery planning. The UPSIDES peer support training consists of 12 core modules: 1) understanding recovery and own recovery journey; 2) tree of life; 3) peer support; 4) communication; 5) recovery planning; 6) activating resources; 7) community and trialogue; 8) problem solving; 9) peer role description; 10) work preparation; 11) recovery groups; and 12) network. Training on local adaptations is provided via additional modules which consider context and address site-specific topics (social and environmental situation, resources in mental health care, stigma, rights and advocacy, trauma and disasters). An online training platform will facilitate exchange among trainers, PSWs and staff members at different study sites, helping to provide cross-site training and supervision while building an international PSW community.

UPSIDES peer support will be provided without hierarchy or judgement, taking into account principles of recovery-oriented care. UPSIDES PSWs will focus on: providing tangible supports; role modelling that recovery is possible; sharing personal experiences of mental health and ill-health; and promoting hope, and a sense of control and opportunities. Specific tasks include: initial assessment of strengths and resources to build on; practical support with daily life as needed (for example, accompaniment for appointments or activities); support during crises; and actively promoting recovery planning. Providing an additional recovery group setting is possible and recommended. UPSIDES peer support will be delivered for up to 6 months, with a minimum of three contacts. Weekly or biweekly meetings are recommended, but frequency may vary depending on the needs of service users, PSWs and study sites. The intervention manual provides additional materials to be used by the PSWs during the intervention. To support the implementation process, organisational readiness workshops are held across trial sites. Participants allocated to the control group (wait list) will start receiving the intervention after completion of follow-up (month 12). Criteria for discontinuing or modifying the intervention include change of content and dose of peer support or PSW in response to participant’s request, harms, or improving or worsening of illness.

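### The 5-year cost-utility model extrapolates well beyond the 12-month randomised comparison, but the sensitivity parameters named for it do not test what is assumed after month 12

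*Protocol article*

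**What the plan says.** All of this is in the protocol article.

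- **Length of support** (Intervention): "UPSIDES peer support will be delivered for up to 6 months, with a minimum of three contacts". The same section says that wait-list controls are offered the intervention once their month-12 follow-up is complete.
- **Data for the economic analysis** (Cost-effectiveness analysis, Measures): service use, productivity losses and EQ-5D are collected from baseline to the 12-month visit.
- **Trial ratio** (Cost-effectiveness analysis, Data analysis): for each country, the difference in mean total costs of illness is divided by "the average QALY difference over 12 months". A bootstrap of 2,000 replications covers sampling uncertainty.
- **Model** (same section): "Results from the primary data incremental cost-utility analysis will be used to develop a decision tree model", whose purpose is "to simulate cost utility and health budget impact of the UPSIDES intervention for each country over a 5-year time frame".
- **Sensitivity analysis of the model** (same section): "The sensitivity analysis will consider variance of programme coverage and equity of service access".

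The article states no assumption about QALY or cost differences after month 12, and no plan to vary one.

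**The concern.** The randomised contrast ends at month 12, both because follow-up stops and because controls may then receive peer support. A 5-year cost-utility simulation built on those data has to assume something about later differences between the arms. Setting them to zero is also an assumption. The trial cannot supply the answer, and a bootstrap of 12-month data cannot show uncertainty about a period that was not observed.

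The two named parameters concern how many people receive support and who they are. They suit the budget-impact half of the model. They do not vary how long a benefit, or a difference in service use and productivity, lasts.

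Value for money is one of the trial's three main objectives, and the article's conclusions say the work is meant to inform policy. The 5-year output is the one closest to a budget decision. If it is produced as described, its stated range could omit an assumption able to move a country across its willingness-to-pay threshold.

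**Working it through.** The article states no 5-year cost per QALY, effect duration or discount rate, so there is no figure to reproduce. The calculation below is an illustration of leverage.

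**Inputs from the article.** Support up to 6 months; costs and QALYs observed for 12 months; model horizon 5 years.

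**Inputs assumed.** Yearly retention of the QALY gain r from 0 to 1; discount rate d of 0%, 3% or 5%; incremental cost C in year 1 only; year-1 QALY gain g.

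**Step 1: share of the horizon without a randomised comparison.** (60 − 12)/60 = 48/60 = 80%.

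**Step 2: single cohort treated once.** The 5-year QALY gain is g × S, where S = Σ (r/(1+d))^k for k = 0 to 4. Cost per QALY is C/(gS), which is 1/S relative to no persistence.

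| Yearly retention r | S, d = 0% | 1/S | S, d = 3% | 1/S | S, d = 5% | 1/S |
|---|---|---|---|---|---|---|
| 0 | 1.000 | 1.00 | 1.000 | 1.00 | 1.000 | 1.00 |
| 0.25 | 1.332 | 0.75 | 1.319 | 0.76 | 1.311 | 0.76 |
| 0.50 | 1.938 | 0.52 | 1.891 | 0.53 | 1.862 | 0.54 |
| 0.75 | 3.051 | 0.33 | 2.926 | 0.34 | 2.849 | 0.35 |
| 1 | 5.000 | 0.20 | 4.717 | 0.21 | 4.546 | 0.22 |

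For example, at 3% and full persistence S = 1 + 0.971 + 0.943 + 0.915 + 0.888 = 4.717. With an assumed $600 and 0.03 QALY in year 1, cost per QALY is 600/0.03 = $20,000 with no persistence and 600/(0.03 × 4.717) ≈ $4,240 with full persistence.

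**Step 3: a new cohort each year, undiscounted.** Five cohorts cost 5C. With no persistence they gain 5g. With full persistence to the end of the horizon they gain (5 + 4 + 3 + 2 + 1)g = 15g. Relative cost per QALY is 5/15 = 0.33, a 3-fold range.

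**Step 4: coverage, for comparison.** Let f be the share of cost at 50% coverage that is fixed. At coverage c, relative cost per QALY is [f + (1 − f)(c/0.5)]/(c/0.5).

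- f = 0: the value is 1.00 at every coverage.
- f = 0.20, c = 25%: (0.20 + 0.80 × 0.5)/0.5 = 1.20.
- f = 0.20, c = 100%: (0.20 + 0.80 × 2)/2 = 0.90.

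**Step 5: persisting cost differences.** The trial ratio uses total costs of illness, so the numerator need not stop at year 1. Split the year-1 difference into a programme cost P, incurred once, and another cost difference D that persists at the same retention and discounting as the QALY gain. Cost per QALY is then (P + D × S)/(g × S) = P/(gS) + D/g. Only the programme part shrinks with persistence. If D is positive, the ratio moves less than in Step 2. If D is a saving, the ratio can change sign. Costs after month 12 therefore need the same treatment as QALYs.

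**The case against.** The strongest reply is that the article is a condensed document. It gives the model one sentence and its sensitivity analysis another, says what the analysis will consider without saying that nothing else will be varied, and a fuller health-economic plan may add persistence scenarios. That stands as a limit. A reader might infer that persistence will certainly go untested, and the text does not establish that. Still, the article does specify the sensitivity analysis, and following it as written would leave the extrapolation unexamined.

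Second, the model structure is not given. A reader might infer that four-fifths of the result rests on an assumed lasting effect. That need not be so: the text fits equally well a programme with new entrants each year who carry only the observed 12-month costs and QALYs. This stands, and it is why Step 3 is shown. Carrying nothing past month 12 remains an assumption that the sensitivity analysis should vary.

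Third, the 5-fold figure is an extreme. It needs one cohort, five years of constant gain and a cost difference frozen after year 1. Step 5 shows that persisting cost differences change the answer. This stands too.

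Fourth, it is tempting to say that coverage cannot affect cost per QALY. That holds only if all costs are proportional to the number treated. Training, readiness workshops and an online platform plausibly have fixed components, so coverage is a legitimate cost-utility parameter.

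Last, a reader might infer that the whole value-for-money objective is at risk. It names no 5-year horizon. The country-level ratios, bootstrap, acceptability curves and net-benefit regressions use the trial's observed data and are untouched.

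**Conclusion.** The point holds, confined to the 5-year simulation. It extends 12-month results over a horizon of which 80% lies beyond the randomised contrast, and the sensitivity parameters named for it do not test the QALY and cost differences assumed for that period.

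Under the illustrative assumptions, cost per QALY varies up to about 4.5- to 5-fold between no and full persistence for a single cohort, about 2-fold between none and 50% yearly retention, and about 3-fold between none and full with yearly cohorts. Coverage from 25% to 100% moves it only between 1.20 and 0.90 times its value at 50% coverage when 20% of cost is fixed. The comparison shows which assumption has the larger leverage in these cases. It does not predict the trial's own range, which depends on effects, costs and a model structure that the article does not give.

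This is a worthwhile, inexpensive improvement to the plan. It is not a defect in the trial's 12-month economic results.

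**What to change.** In the Data analysis section of the cost-effectiveness analysis:

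1. State what the 5-year model assumes about QALY and cost differences after month 12.
2. Add persistence of both as a named sensitivity parameter, with three scenarios: none, waning and full.
3. Report these scenarios for each country beside the 12-month result, ideally with the duration of effect at which the country's willingness-to-pay threshold is just met.
4. Keep coverage and equity of access as further parameters.

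A base case with no effect after month 12 is one reasonable choice but need not be mandated. It is conservative only where support costs more and gains QALYs.

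The cost is a sentence or two and a few extra model runs, with no new data. The downside is that the reported 5-year ranges will be wider.

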### Process evaluation

Participants in the process evaluation include service users, PSWs, mental health workers and other key informants involved in the UPSIDES intervention. PSWs and service users will be recruited from the participants in the randomised controlled trial (see above). Purposive sampling strategies will be applied for mental health workers and key informants. Mental health workers will be recruited from multidisciplinary teams who cooperate with PSWs. Key informants will be local stakeholders with relevant expertise relating to implementation of peer support work, including clinicians and managers who employ PSWs.

